### Statistical analysis

To demonstrate the data, the results were described as mean ± standard deviation, median and interquartile range and percentage values. To calculate the cost of the dual task, the formula was used: [(TUG DT performance – TUG performance)/ TUG performance * 100 %] [29].

Initially, the Shapiro-Wilk test will be performed to assess the normality of the data and the Levene test to assess homogeneity. When the data did not show homogeneity of variances, the Welch test correction will be applied in the main analyses.

To analyze the characteristics of the groups, the *X*^2^ test and unpaired t student's test will be used. To analyze the primary and secondary outcomes, ANOVA two-way (between-within factors) *post hoc* Tukey will be used. To analyze the effect size of the unpaired t student's test Cohen's D will be used and to analyze the size of ANOVA two-way Cohen's F group will be used, and will be used the G*Power 3.1 software (University of Dusseldorf, Dusseldorf, Germany). For Cohen's F (Cohen's D), up to 0.10 (0.20) will be accepted as a no effect size, 0.11 – 0.24 (0.22 – 0.49) as a small effect size, 0.25 – 0.35 (0.50 – 0.70) as a moderate effect and equal to or greater than 0.40 (0.80) as a strong effect size. The intervention effect will be calculated based on intention-to-treat analysis. Values *p* < 0.05 were accepted as significant. The software used will be Jamovi 2.3 software (Jamovi project, Sydney, Australia) and Graphpad Prism 9.0 software (Graphpad, California, USA).

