## Sample size and subject recruitment

For the sample calculation, the primary outcome was the total MiniBESTest value. The value of the minimum clinically significant difference is 3.4 points in the total MiniBESTest value [18]. Using this value, for the statistical calculation of ANOVA two-way (between-within factors) an effect size of 0.25 Cohen's F was found. Therefore, we calculate using an effect size of 0.25 Cohen's F, type I error (alpha) of 5 %, type II error (beta) of 80 %, 2 groups, 3 moments (before training, after training and follow-up) and a correlation between repeated measurements of 0.5. After the calculation we arrived at the value of 14 patients per group. Accepting the possibility of 20 % possible sample loss, the selection of 17 patients per group was considered. For the calculation, the statistical software G*Power 3.1 (Universitat Kiel, Kiel, Germany) was used.

Community-dwelling people with PD will be recruited from the general community, by means of advertisements and by screening reference outpatient clinics. Participants of both sexes will be included, regardless of age, with a clinical diagnosis of PD, classified as 3 or 4 Hoehn & Yahr scale [19], and who agreed to participate in the study with consent. Individuals with neurological disorders other than PD and with cognitive deficits that prevented them from carrying out the assessments were not included, and individuals with scores lower than 8 on the 10-CS were not included [20]. The study was written based on the CONSORT checklist [21] and included a total of 4 stages: Initial assessment (AV1), Intervention, Immediate Post-intervention Assessment (AV2) and Reassessment (follow-up) (Fig. 1). After providing a signed consent form, individuals were invited to participate in the assessment and intervention protocols described below.

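### The Levene-triggered Welch correction is not defined for the between-within ANOVA it is attached to, so the primary group-by-time test is left open in that branch

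*Protocol article*

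**What the plan says.** The Statistical analysis section lists two assumption checks: "the Shapiro-Wilk test will be performed to assess the normality of the data and the Levene test to assess homogeneity". It then fixes a remedy for the second: "When the data did not show homogeneity of variances, the Welch test correction will be applied in the main analyses".

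The analysis this refers to is named in the same section: "To analyze the primary and secondary outcomes, ANOVA two-way (between-within factors) *post hoc* Tukey will be used". The only tests in the section to which a Welch correction applies directly have another purpose: "To analyze the characteristics of the groups, the *X*^2^ test and unpaired t student's test will be used".

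The section on sample size names the total MiniBESTest as the primary outcome. It plans for "2 groups, 3 moments (before training, after training and follow-up" and assumes "a correlation between repeated measurements of 0.5". Sphericity and its corrections are not mentioned anywhere in the article.

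**The concern.** The ordinary Welch correction replaces the pooled variance when independent group means are compared. A between-within ANOVA tests group by time against a within-subject error term pooled over groups and moments, and the ordinary correction does not say what replaces that term. So when Levene is significant, the text names a remedy but no test.

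Several substitutes are possible: Welch t tests at each moment, Welch t tests on change scores, or a Welch-James approximate-degrees-of-freedom test of the interaction. They answer different questions and can give different p values. The choice would be made with the data in hand, for the primary outcome as well as the secondary ones.

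The remedy is also aimed at only one of two variance assumptions. With three moments, the interaction F test also needs sphericity, which neither Levene nor Welch addresses.

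**Working it through.** **1. Which effect the sample size refers to.** Inputs from the sample size section: Cohen's f 0.25, alpha 0.05, 2 groups, 3 moments, correlation 0.5. The 80% printed there as type II error is read as power. For the within-between interaction:

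- λ = f² · N · m · ε / (1 − ρ)
- df1 = (k − 1)(m − 1)ε
- df2 = (N − k)(m − 1)ε

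With N = 28 and ε = 1: λ = 0.0625 × 28 × 3 / 0.5 = 10.5, df = 2 and 52, power 81.2%. N = 26 gives 77.8%. So 28 in total, 14 per group, reproduces the stated figure. The between-groups main effect would need N = 86, and power of 20% would need only N = 8. The planned test is therefore the group-by-time interaction, with sphericity assumed.

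**2. Does Welch define that test?**

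| Test named in the article | Used for | Ordinary Welch version |
|---|---|---|
| Unpaired t test | group characteristics | yes |
| Two-way between-within ANOVA | primary and secondary outcomes | none defined for group by time |

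The correction is assigned to the second row.

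**3. Non-sphericity.** The article gives no epsilon, so the correlation patterns here are assumptions. Take equal variances, correlation a between baseline and each later moment, and b between the two later moments. The two contrast variances are l1 = 1 − b and l2 = 1 − (4a − b)/3, and ε = (l1 + l2)² / [2(l1² + l2²)].

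- a = b = 0.5 (the article's single value): l1 = l2 = 0.5, ε = 1
- 0.5/0.8: l1 = 0.2, l2 = 0.6, ε = 0.64/0.80 = 0.80
- 0.3/0.9: l1 = 0.1, l2 = 0.9, ε = 1/1.64 = 0.61

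Simulated type I error of the interaction test at nominal 5% (100,000 null trials per scenario):

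| ε | 14 per group, uncorrected | Greenhouse-Geisser | 17 per group, uncorrected | Greenhouse-Geisser |
|---|---|---|---|---|
| 1 | 5.0% | 4.6% | 5.1% | 4.7% |
| 0.80 | 6.0% | 4.9% | 6.1% | 4.9% |
| 0.61 | 7.5% | 5.0% | 7.4% | 5.0% |

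Separate runs of the same scenarios at 14 per group gave up to 7.6%, hence the range of about 6.0% to 7.6%.

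**4. Power of the corrected test at ε = 0.7.** For N = 28: λ = 10.5 × 0.7 = 7.35, df = 1.4 and 36.4, power 70.0%. For N = 34: λ = 12.75 × 0.7 = 8.925, df = 1.4 and 44.8, power 79.0%. With ε = 1 and N = 34, power is 88.8%.

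**5. Unequal variances, the case the rule is meant for.** Correlation 0.5, assumed variance ratios, no correction:

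| Completers | Ratio 2 | Ratio 4 |
|---|---|---|
| 17 against 17 | 5.0% | 5.3% |
| 14 against 17, larger group more variable | 4.1% | 3.7% |
| 14 against 17, smaller group more variable | 6.1% | 7.2% |

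Losing 3 of 17 in one arm is 18%, within the 20% loss the article allows for. At ratio 4 with 14 against 17, Greenhouse-Geisser gives 3.4% and 6.6%, so it does not remove this distortion.

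**The case against.** The strongest case against has four parts.

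- **The rule could be carried out.** A reader might infer that no Welch procedure is possible here. That goes too far: Welch-James tests exist for split-plot designs, and Welch tests can be run per moment or on change scores. What stands is that the article picks none of them. Reading the sentence as covering only the unpaired t tests is strained, because it speaks of the main analyses and those t tests serve group characteristics.
- **Silence on sphericity is not an error in a journal article.** A reader might infer that sphericity will be neither checked nor corrected. The article does not say so, and a full plan may deal with it. That part of the objection is accepted. The finding rests on the remedy that is stated, which does not fit the stated model.
- **The figures rest on assumptions.** This is correct. The only correlation given implies ε = 1 under equal variances, and nothing in the article shows that the two later moments correlate more strongly. The inflated type I error and the lower corrected power are also alternatives: the first arises without correction, the second with it.
- **The rule has little numerical effect in the planned design.** This is true at 17 against 17. It is not true once completers are unequal.

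**Conclusion.** The point holds as a defect of specification. If Levene is significant, the article does not determine the primary group-by-time test, and the gap would be filled after the data are seen. That conclusion needs no numerical assumption.

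The size of the related risk is moderate and conditional. If sphericity fails (ε 0.80 to 0.61, assumed) and is left uncorrected, type I error is about 6.0% to 7.6% rather than 5%. If it is corrected at ε = 0.7, power is 70% with 28 and 79% with 34 participants. Unequal variances distort the test mainly when completers differ between arms: about 3.7% or 7.2% at ratio 4, depending on which arm is more variable.

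The documents do not support the stronger conclusions that the trial's primary test has an inflated error rate, or that sphericity is the only assumption that matters. The true epsilon and variance ratio are unknown, and unequal variances can matter too.

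**What to change.** 1. Restrict the Welch correction to the unpaired t tests.
2. Remove the Levene-triggered switch from the analysis of the primary outcome.
3. State in advance that the primary test is the Greenhouse-Geisser-corrected group-by-time interaction, whatever the pre-tests show.
4. If a mixed model with unstructured covariance is preferred, name Kenward-Roger or a similar small-sample degrees-of-freedom method. Without one the replacement is no better than the problem: a Wald chi-square test of the interaction had simulated type I error of 7.5% at 14 and 7.0% at 17 per group, and an uncorrected robust variance gave 8.7% and 8.0%.
5. If unequal variances with unequal completers are a real worry, specify group-specific covariance in that model, because Greenhouse-Geisser does not deal with them.

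The cost is wording only, with no added participants or visits. If sphericity does hold, the corrected test is slightly conservative (type I error about 4.6% to 4.8% instead of 5%), with a correspondingly small loss of power.

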The cerebellum plays a relevant role in motor control [15]. It is related to the control of the vestibular system, proprioception, cognition and motor programming, receiving visual and auditory input and sending efferent fibers to the thalamus, red nucleus and cortex (motor, pre-motor and pre-frontal cortex) [16]. tDCS has been widely used in the motor cortex, however, Mello [17] suggests that applying tDCS in the cerebellar region could be an alternative to stimulate the efferent pathways of the cerebellum to act on the cortical structures involved in motor processing and, in this way, influence the motor learning process [17].

Therefore, the objective of the present study is to investigate the effects of a balance training program associated with cerebellar tDCS on postural control in individuals with PD.

The specific research questions are:•In people with Parkinson's Disease, is balance training associated with tDCS superior to balance training alone for improving walking (balance, postural control), mobility and falls?•Are any benefits maintained beyond the intervention period?

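### The primary MiniBESTest analysis names no deciding between-group test and treats baseline as an outcome level; one baseline-adjusted contrast would repair both cheaply

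*Protocol article*

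**What the plan says.** The protocol article fixes the following.

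- Outcome (Sample size and subject recruitment): "the primary outcome was the total MiniBESTest value".
- Model (Statistical analysis): "To analyze the primary and secondary outcomes, ANOVA two-way (between-within factors", with Tukey as the post hoc method and p < 0.05 as the threshold. The same model serves all secondary outcomes.
- Time levels (Sample size and subject recruitment): "3 moments (before training, after training and follow-up". The pre-treatment score is therefore a level of the response.
- Questions (Background): whether adding tDCS to balance training is superior to training alone, and separately "Are any benefits maintained beyond the intervention period".

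The text does not say whether the group effect, the time effect, the interaction or a Tukey pair answers the superiority question, or at which visit. It mentions no adjustment for the baseline score.

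**The concern.** A two-group, three-visit mixed ANOVA produces three F tests, and they answer different questions.

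- The time effect can be significant from training alone, because both arms train.
- The group effect averages in a visit before treatment, where randomisation makes the expected difference zero.
- Only the interaction tests differential change. It is an omnibus test and does not by itself say at which visit the groups differ.

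If Tukey is then run over all six group-by-visit cells, there are 6 × 5 / 2 = 15 pairs. Only three compare EG with PG at the same visit, and one of those three is baseline.

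Two things are at stake. Several different p < 0.05 results could be presented as the trial's answer. And the comparison most readers will look for, EG against PG after training, could be read from a test with far less power than the sample-size section suggests. The baseline MiniBESTest could sharpen that comparison as a covariate, but is not used that way.

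**Working it through.** **Inputs from Sample size and subject recruitment.** f = 0.25 ("an effect size of 0.25 Cohen's F was found"); alpha 5%; 2 groups; m = 3 visits; correlation ρ = 0.5; 14 per group (N = 28), raised to 17 (N = 34). The text gives "type II error (beta) of 80" %. Only power of 0.80 reproduces the sample size, so I read it that way.

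**Step 1: the plan's own figure.**
- Interaction: λ = f²·N·m/(1−ρ) = 0.0625 × 28 × 3 / 0.5 = 10.5, on 2 and 52 df. Power is 0.812; at N = 26 it is 0.778. So 14 per group reproduces.
- Time effect: same λ and df, hence the same N.
- Group effect: λ = f²·N·m/(1+2ρ) = 0.0625 × 28 × 3 / 2 = 2.625. Reaching 80% would need N = 86.

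**Step 2: what f = 0.25 means for EG minus PG.** Assumptions not in the document: a group difference over the three visits of (0, d, d) or (0, d, 0), compound symmetry and complete data. For both patterns the interaction f equals d/√18 in SD units, so d = 0.25 × √18 = 1.06 SD. No SD is given. If d is the stated 3.4 points, the SD is 3.4 / 1.06 ≈ 3.2.

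**Step 3: power at ρ = 0.5, with n per group.**
- Baseline-adjusted contrast after training: SE = √[(1−ρ²)·2/n]. At n = 14 this is √(0.75 × 2/14) = 0.327, so the noncentrality is 1.06/0.327 = 3.24 and power is 0.876 on 25 df.
- Unadjusted contrast: SE = √(2/14) = 0.378, power 0.771. An unadjusted change score has the same power at ρ = 0.5, so the gain comes from covariate adjustment.
- Group main effect: SE = √[(1+2ρ)/3 · 2/n] = 0.309. The mean difference is 2d/3 for (0, d, d) and d/3 for (0, d, 0).
- EG–PG pair after training in a six-cell Tukey table: critical t 2.96 instead of 2.01; power from 20,000 simulated trials per scenario.

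| Test | N = 28 | N = 34 |
|---|---|---|
| Interaction F | 0.81 | 0.89 |
| Baseline-adjusted EG–PG after training | 0.88 | 0.93 |
| Unadjusted EG–PG after training | 0.77 | 0.85 |
| Six-cell Tukey, EG–PG after training | 0.45 | 0.56 |
| Group main effect, (0, d, d) | 0.60 | 0.69 |
| Group main effect, (0, d, 0) | 0.20 | 0.23 |

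Simulation puts the adjusted contrast slightly lower than the formula: 0.86 at N = 28 and about 0.92 at N = 34. By formula it reaches 80% at N = 24, so the planned sample remains adequate.

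**Step 4: sensitivity.** For the same two patterns at N = 28, interaction against adjusted contrast is 0.962 against 0.965 at ρ = 0.7, and 0.996 against 0.994 at ρ = 0.8. For a partly fading benefit (0, d, d/2), f = 0.25 implies d = 1.22 SD. At ρ = 0.5 and N = 28 the adjusted contrast then has 0.95, the interaction 0.81 and the Tukey pair 0.61.

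**Step 5: type I error if two tests could each count.** If a significant group effect or a significant interaction were accepted, independence gives 1 − 0.95² = 0.0975. Simulation under no effect gives 0.095 at N = 28 and 0.098 at N = 34.

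**The case against.** The best defence is that the planned analysis is valid. In a randomised trial the interaction in a mixed ANOVA is an unbiased test of differential change, and the sample size matches it. Against that test, baseline adjustment gains about 6 points of power at N = 28 and 4 to 5 at N = 34, and nothing at correlations of 0.7 to 0.8. The article is also condensed, and a separate analysis plan may name the deciding contrast and the Tukey family. All of this stands, and it limits the point to an improvement. It does not remove it, because the article itself fixes model, post hoc method and threshold, and that choice does not map either research question to a test.

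A reader might go further in four ways that the document does not support.

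- That the 14 per group proves the interaction was meant. The time effect gives the same N.
- That the trial's power is only 45%. The text does not say that Tukey runs over six cells, or that one Tukey pair decides.
- That the trial's type I error is nearly 10%. No sentence allows either of two tests to count; the figure shows only what the silence would permit.
- That the group effect has 34% power. That sets the group effect's own f to 0.25, a different scenario. Under the patterns used here it is 0.60 or 0.20.

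**Conclusion.** The point holds as a should-fix. The article leaves open which effect and which visit decide the superiority question, and it uses baseline as an outcome level where it would serve better as a covariate. The first matters more, because it determines what counts as a positive result. The power gain over the interaction test is small and depends on the correlation. The loss is large only if the result is read from a six-cell Tukey table or from the group main effect. These sizes rest on the plan's f and on the assumptions declared in the working: the time pattern of the difference, compound symmetry, complete data and the Tukey family. The SD of 3.2 is only the value that links 3.4 points to f = 0.25.

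**What to change.** State one primary test: the EG minus PG difference in total MiniBESTest at the immediate post-intervention assessment (AV2), adjusted for the initial assessment (AV1) score, two-sided at 5%. Take it from a model that also yields the adjusted follow-up difference, and make that the secondary test for the maintenance question. Drop Tukey over the six cells, keep within-group changes descriptive, and adjust each secondary outcome for its own baseline value.

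The cost is a change of wording in the analysis section, with no new patients, visits or measurements. The small downside is that the omnibus interaction, which the sample size reproduces, is no longer the headline test. The Protocol validation section reports that data analysis is ongoing, so the change should be dated, with a statement of whether results by group had already been seen.

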**Table utbl0001:** 

Subject area:	Neuroscience
More specific subject area:	**TRANSCRANIAL DIRECT CURRENT STIMULATION (tDCS) ASSOCIATED WITH BALANCE TRAINING IN INDIVIDUALS WITH PARKINSON'S**.
Name of your protocol:	**EFFECTS OF TRANSCRANIAL DIRECT CURRENT STIMULATION (tDCS) ASSOCIATED WITH BALANCE TRAINING IN INDIVIDUALS WITH PARKINSON'S: STUDY PROTOCOL FOR A RANDOMIZED CLINICAL TRIAL**
Reagents/tools:	tDCS: Neuromodulator from Microestim Foco Research, NKL, Santa Catarina, Brazil. Baiobit Movement Analysis® (BTS Bioengineering S.P.A., Italy) All acceleration data will be recorded by sampling at 100 Hz frequency, transmitted to a notebook via Bluetooth and processed by the Rivelo software program (BTS Bioengineering Group, S.P.A., Italy
Experimental design:	A prospective, randomized controlled trial with concealed allocation, blinded assessors (participants and therapists), and intention-to-treat analysis will be carried-out (Figure 1). Community-dwelling people with PD will be recruited from the general community, by means of advertisements and by screening reference outpatient clinics. Participants of both sexes will be included, regardless of age, with a clinical diagnosis of PD, classified as 3 or 4 Hoehn & Yahr scale^18^, and who agreed to participate in the study with consent. Individuals with neurological disorders other than PD and with cognitive deficits that prevented them from carrying out the assessments were not included, and individuals with scores lower than 8 on the 10-CS were not included^19^
Trial registration:	Brazilian Registry of Clinical Trials (RBR-52y3zgd
Ethics:	The study was conducted in line with recommendations from the Declaration of Helsinki and received ethical approval from the Ethics Committee of the Federal University of the Amazonas, Brazil [CAAE 54,743,121.5.0000.5020].
Value of the Protocol:	Cerebellar tDCS associated with balance training may help improve postural control and balance in walkers with Parkinson's Disease. The hypothesis is, if walking improve, the benefits may be accompanied by better balance and reduced fear of falling, and individuals may experience greater free-living physical activity at home and in the community. The goal of protocol is to investigate the effects of balance training associated with cerebellar tDCS on postural control in individuals with PD.

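### Intention-to-treat is promised, but the three-visit between-within ANOVA does not by itself deliver it once a visit is missed

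*Protocol article*

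**What the plan says.** Two places in the protocol article fix the analysis population. The specifications table, under experimental design, states that "intention-to-treat analysis will be carried-out", and the Statistical analysis section repeats it: "The intervention effect will be calculated based on intention-to-treat analysis".

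The same section names one method for all efficacy outcomes: "To analyze the primary and secondary outcomes, ANOVA two-way (between-within factors"), with Tukey post hoc comparisons. The section on sample size and recruitment states that "the primary outcome was the total MiniBESTest value" and gives the within factor as "3 moments (before training, after training and follow-up"). It arrives at 14 per group, then allows for 20% loss: "possible sample loss, the selection of 17 patients per group was considered".

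No imputation is mentioned, and no method that can use an incomplete record.

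**The concern.** The article makes two positive statements, a population and a method, and they fit together only if nobody misses a visit or missing scores are filled in. A classical between-within ANOVA needs a value in every within-subject cell. Run as named, it removes any participant without an AV2 or follow-up score. Someone who attended AV2 and missed only the follow-up also loses the AV2 score.

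Such exclusions happen after randomisation and may depend on how the participant responded. The Limitations section itself says that the interventions depend on motivation and adherence. If the reasons for leaving differ between the arms, the groups compared are no longer the randomised ones, yet the result would carry the intention-to-treat label.

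**Working it through.** **1. The plan's own sample size.** Inputs from the sample-size section: "we calculate using an effect size of 0.25 Cohen's F", "type I error (alpha) of 5" %, 2 groups, 3 moments, correlation 0.5, and a target of 80% that the text labels beta but that must be read as power. For the group-by-time interaction, with sphericity:

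- Noncentrality λ = N·m·f²/(1−ρ), with df1 = (k−1)(m−1) = 2 and df2 = (N−k)(m−1).
- At N = 28: λ = 28 × 3 × 0.0625/0.5 = 10.5, df2 = 52, power 0.812. This is the smallest even N that reaches 0.80, so 14 per group reproduces.
- The between-group main effect would need 86 in total, so the interaction is the test that was sized.
- Allowance for loss: 14 × 1.2 = 16.8, rounded up to 17 per group, 34 in total.

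**2. Number excluded at the allowed loss.** 34 × 0.20 = 6.8, leaving 27.2 complete participants. Counting instead down to the 28 that were sized, 34 − 28 = 6. So about 6 to 7 of 34 leave the analysis.

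**3. Power of the planned interaction test by number of complete participants.**

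| N analysed | λ | Power |
|---|---|---|
| 27 | 10.125 | 0.795 |
| 28 | 10.5 | 0.812 |
| 34 | 12.75 | 0.888 |

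The last row is an upper bound for any method that keeps partial records, because partial records carry less information than full ones. If participants can miss either post-baseline visit independently, the share with complete data is (1−p)². For p = 5%, 10%, 15% and 20% per visit, about 31, 28, 25 and 22 participants remain, with power 0.854, 0.812, 0.760 and 0.697.

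**4. Possible bias.** The article gives no SD and no dropout mechanism, so what follows is illustration. Assumptions: true difference in change to AV2 of 3.4 points (the minimum important difference in the sample-size section), SD 3.2, correlation 0.5, 17 per arm, and departures after AV2. The SD of change is 3.2 × √(2 × (1−0.5)) = 3.2. When the k least-improved of 17 leave, the mean change of those who stay rises by a multiple of that SD: 0.207 for k = 2, 0.295 for k = 3 and 0.463 for k = 5 (simulated normal order statistics).

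| Who leaves after AV2 | Completers' difference at AV2 |
|---|---|
| 3 least-improved in each arm | 3.4 |
| 5 EG and 2 PG, leaving only weakly related to response (correlation 0.3) in both arms | 3.6 |
| 5 and 2 least-improved in EG and PG | 3.4 + 3.2 × (0.463 − 0.207) = 4.2 |
| 3 least-improved in EG, 3 at random in PG | 3.4 + 3.2 × 0.295 = 4.3 |
| 5 least-improved in EG, 2 at random in PG | 3.4 + 3.2 × 0.463 = 4.9 |

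At an assumed SD of 5 the last row becomes 3.4 + 5 × 0.463 = 5.7. In every row, all 34 AV2 scores taken together give 3.4 on average, because in these scenarios each participant has an AV2 score. The direction is not fixed: if the selective loss were in PG, the sign of the bias would reverse.

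**The case against.** **Imputation would reconcile the two statements.** Intention-to-treat and a between-within ANOVA are compatible if missing scores are imputed, and a condensed article may leave that to a fuller plan. This stands as a limit on the claim: the documents do not show that participants will be dropped, only that the named method drops them unless something is added. It does not remove the point, because the method is the only one stated and does not deliver the stated population.

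**The increase from 14 to 17.** A reader might infer that it confirms an intended completers analysis. It does not. Dropout costs information under any method, so trials with full intention-to-treat analyses inflate too, and the text speaks of a possible loss, not of an exclusion.

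**Power.** A reader might also infer a serious loss of power. For the interaction that was sized, the allowance does its job: power is about 0.80 at the allowed loss. A baseline-adjusted AV2 contrast would show a different drop, but the protocol plans no such contrast.

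**Bias.** The 4.9 is an adverse case, with selective loss in one arm only. With the same pattern and number in both arms the bias is about zero. The Limitations section also plans contracts and phone calls to support compliance.

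**The remedy has limits.** The recovery of 3.4 depends on AV2 being observed. If participants leave during the four weeks of training, AV2 is missing too. A mixed model with baseline only as a covariate would then omit them, so that form would not be full intention-to-treat either.

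**Conclusion.** The point holds as a mismatch between population and method: the promised intention-to-treat analysis is not delivered by the ANOVA as named when AV2 or follow-up is missing. At the allowed 20% loss, 6 to 7 of 34 participants would be excluded, with their observed visits. The harm is mainly possible bias under an intention-to-treat label, plus wasted data; power is secondary. The size of the bias cannot be known from the article. The 3.4 to 4.9 points rest on an assumed SD of 3.2, a correlation of 0.5 and chosen dropout patterns that favour EG or are neutral. The exclusion itself rests on the absence of imputation, which a fuller plan could supply. Severity: should-fix.

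**What to change.** For the primary outcome, replace the between-within ANOVA with a linear mixed model fitted by REML with unstructured covariance. Use every available MiniBESTest score of every randomised participant, in the allocated group. Keep baseline as one of the three repeated outcomes, with its mean constrained equal across groups, so that participants with no post-baseline score are also included; they add little information on the treatment effect, but no one randomised is left out. State the missing-at-random assumption, and keep the complete-case ANOVA as a sensitivity analysis. Multiple imputation before the ANOVA, by allocated group, is an acceptable alternative if it is written down.

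The Protocol validation section says that data analysis is under way, so the change should be documented and dated before any comparison by group is seen.

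Cost: revised wording in the Statistical analysis section and slightly more analysis work, with no extra patients or data. The downside is reliance on missing-at-random, which the data cannot confirm.
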